### Randomization and Allocation

Following the signing of a consent form, participants are allocated in a 1:1 ratio to either ePROs-based group or control group based on the computer-generated random. Group numbers were sealed into the non-transparent envelopes kept by a specially appointed person. Because of the nature of interventions, the blinding of participants and investigators is impossible. But the data collectors who help to administer ePROs collection will be blinded to group allocation.

### Intervention and Control

The primary early advantage of the ePROs applet development process was the product development based on the human-centered design (HCD) philosophy and two-drill design model. Stakeholders including children, parents, researchers in related fields, clinical medical staff, software engineers, and so on were included. Sufficient demand mining was carried out through qualitative research methods to ensure the scientific nature of information system product design in the stage of “discovery” and “definition.” In the whole process of “development,” the agile software development method is adopted, that is, the gradual development of modules and functions is completed, and the results of the development team are tested after the initial completion of each module development, and the vulnerabilities are corrected immediately, so that the software is always in the state of trial and operation in the development process. Under the continuous iteration of module development and testing, overall development and testing, the final development of the product was completed. ePROs give full consideration to the children's users these specific population characteristics, such as cartoon interface, voice assistant function, games, incentive function, and so on.; at the same time, the content, and function of development are the combination of theoretical research, literature research, expert consultation, and so on, so the final small program overall harvest in the usability test users more positive evaluation.

After enrollment, investigators help the patients develop a WeChat mini-program (ePROs) by scanning the code, and the participants are instructed on how to use the ePRO. They are required to complete the first ePROs questionnaires (including demographic questionnaire, PedsQL^TM^3.0-RM, and C-Ped-PROMIS) during hospitalization (baseline, typically within 48 h after admission). The patient disease-associated questionnaire was filled out by the investigator before the patients were discharged from hospital. The follow-up period is 12 months, and we will collect the ePROs questionnaires at four time points (1, 3, 6, and 12 months after discharge). Then, 1 week before these four scheduled time points, a WeChat reminder message was sent to patients automatically to remind them to complete the PedsQL^TM^3.0-RM and C-Ped-PROMIS. If they do not respond within the scheduled time, we will send a reminder message again. If they still do not respond within 2 days after reminding, a telephone follow-up within 24 h will be conducted. Patients who did not answer after three phone calls within 24 h were considered “lost to follow-up,” and they were censored at the last follow-up date.

ePROs-based group will receive symptom management, the specific process as follows: when there are one or more one C-Ped-PROMIS items exceed the preset intervention threshold (T-scores ≥50), the “early warning symptom” will be triggered. The investigators will receive real-time warning information on WeChat, and they will generate some interventions based on the reported scores and send it to the patient through the “symptom intervention” module. Interventions are developed by a multidisciplinary team (including rheumatologists, specialist nurses, therapists, and others) based on the clinical experience and updated clinical practice guidelines. The control group will only fill in the ePROs questionnaires and do not trigger the “early warning symptom.” During hospitalization, the doctors and nurses manage symptoms based on their judgment rather than the scores of C-Ped-PROMIS. After discharge, they will imply the standard symptom interventions according to the patients' disease condition and treatment effects. Patients are suggested to contact the clinical team immediately in case of serious impairments.

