### Sample Size Calculation

Sample size was calculated using the primary outcome –Pediatric Patient Reporting outcomes (Profile 25), and the “two mean comparison formula” as follows (35, 36): $n_{2}=\frac{{\left(z_{1-\alpha /2}+z_{1-\beta }\right)}^{2}(sd_{1}{}^{2}+sd_{2}{}^{2})(1+1/k)}{2{\left(mean_{1}-mean_{2}\right)}^{2}}$, *n*_1_ = *k*×*n*_2_, was used for the calculation. Z_1−**α**/2_ = 1.96, Z_1−**β**_= 0.84, according to the pre-experimental results, the mean ± standard deviation ($\overset{-}{\chi }$ ± SD) of ePRO group is 50 ± 10, and the ($\overset{-}{\chi }$ ± SD) of the control group is 43 ± 10. Taking into account the dropouts and lost follow-up rate of about 20%, we will finally enroll 50 participants in each group.

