### Outcomes and Measurement

#### Primary Outcome

The primary outcome of this study is the mean T-scores of patients in the ePROs-based group and the control group. The C-Ped-PROMIS is the primary ePRO tool, and it has eight short forms for assessing the child's symptoms and quality of life during the previous 7 days. Each form has a single dimension, and the 5-level Likert scoring method scale with the answers “never” (0) and “almost” always (4) is used for each item. Raw scores of each form are converted to standardized T-scores with a mean of 50 and a standard deviation of 10. Only all forms are answered completely and performed this conversion.

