### Statistical Analyses

SPSS 20.0 will be used for statistical analysis. Intention-to-treat analyses will be conducted by including all available data in the analysis. Missing data will be imputed by the multiple imputation method. A two-sided *p* < 0.05 is considered to be statistically significant. Data are first subjected to the normality tests, continuous variables that conformed to the normal distribution will be presented as the mean (SD), and do not conform to a normal distribution will be expressed as median (IQR). Categorical variables will be presented as frequencies or proportions. Comparisons between groups will be conducted using the Wilcoxon and Fisher's exact tests. Trajectories of PROs will be compared in two groups by repeated measures ANCOVA, as implemented under the general linear model. The MPLUS will be used to sort and analyze the data, and the LTA model was used to evaluate the intervention effect. In addition, subgroup analysis was carried out according to subgroups of JIA.

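### One unreachable episode at a single time point makes a child lost to follow-up and censored, with no stated return, which read literally conflicts with an analysis of all available data

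*Protocol article*

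**What the plan says.** Intervention and Control schedules questionnaires at 1, 3, 6 and 12 months after discharge. An automatic message goes out a week before each time point and a second message follows non-response. After two more days without an answer, the family is telephoned. The sequence ends: "Patients who did not answer after three phone calls" within 24 h are treated as lost to follow-up, "and they were censored at the last follow-up date". Nothing is said about a child coming back at a later time point.

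Primary Outcome describes eight short forms. Each has one dimension, and each form's raw score is converted to its own T-score. The completeness condition reads: "Only all forms are answered completely and performed this conversion".

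Statistical Analyses states: "Intention-to-treat analyses will be conducted by including all available data in the analysis". It adds that missing data will be multiply imputed.

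**The concern.** The loss rule is triggered by one 24-hour window at one time point. If that happens at month 1, the assessments at months 3, 6 and 12 are still to come. Censoring belongs to time-to-event data, and this trial has no such endpoint: the outcomes are T-scores and quality-of-life scores at fixed visits. The ordinary operational reading is that data collection stops there, which is hard to square with analysing all available data. An analysis plan cannot repair this, because a questionnaire never requested cannot be recovered. Imputation keeps the child in the analysis, but only by putting model-based values in place of ones that could have been collected.

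The scoring sentence raises a related problem. Read literally, one incomplete form blocks conversion of the other seven, although none of them needs it. The PedsQL rheumatology module, under Secondary Outcomes, is scored by dividing by the number of answered items and so does use partial responses.

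At stake are observed data on the primary outcome, mostly late in follow-up, in a trial whose Discussion already worries about response over one year.

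**Working it through.** **1. The plan's own sample size.** Inputs from Sample Size Calculation: z = 1.96 and "0.84, according to the pre-experimental results"; the mean "of ePRO group is 50 ± 10" and the mean "of the control group is 43 ± 10", so difference 7 and SD 10; k = 1.

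n = (1.96 + 0.84)² × (100 + 100) × 2 / (2 × 7²) = 7.84 × 400 / 98 = 32.0 per group.

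With 20% loss: 32 / 0.8 = 40 per group. The stated 50 is not reproduced. The excess is conservative, and the present point does not depend on it. The 32 serves below as the number needed with observed data.

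**2. Retention at month 12 under two readings.** Let p be the chance, at each visit, that a child is still unreachable after both messages and all three calls. The document gives no such rate, so p is an assumption, taken as independent across visits and equal in both arms. Month 12 is used because loss is largest there.

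- One miss ends follow-up: retention = (1 − p)⁴.
- Return allowed: retention = 1 − p.
- Power with n observed per arm: Φ(7 / (10 × √(2/n)) − 1.96), with 50 enrolled per arm.

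| p per visit | Retained, one miss ends follow-up | n per arm | Power | Retained, return allowed | n per arm | Power |
|---|---|---|---|---|---|---|
| 2% | 92% | 46.1 | 0.919 | 98% | 49.0 | 0.934 |
| 5% | 81% | 40.7 | 0.885 | 95% | 47.5 | 0.927 |
| 10% | 66% | 32.8 | 0.809 | 90% | 45.0 | 0.913 |
| 15% | 52% | 26.1 | 0.715 | 85% | 42.5 | 0.897 |

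Worked line for 10%: 0.9⁴ = 0.656; 50 × 0.656 = 32.8; 7 / (10 × √(2/32.8)) = 2.83; 2.83 − 1.96 = 0.87; Φ = 0.81.

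**3. When the planned loss is used up.** 1 − (1 − p)⁴ = 0.20 gives p = 1 − 0.8^(1/4) = 0.054, or about 5.4% per visit.

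**4. The scoring sentence, only if it means all eight forms.** If each form is complete with an assumed, independent probability q, all eight are complete with probability q⁸: 0.99⁸ = 92%, 0.98⁸ = 85%, 0.95⁸ = 66%.

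**5. The text side by side.** Intervention and Control ends a child's follow-up in words that fit survival data and gives no way back. Statistical Analyses promises to use whatever is available. The two agree only if censoring merely records the date of last contact, and the document does not say so.

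**The case against.** A reader might infer that missing a single questionnaire makes a child lost. The document does not support that: two messages and three calls come first, and a late responder who picks up the telephone is not lost.

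A reader might also infer that valid later data are discarded. That is not stated. No section says that a later questionnaire is refused, that reminders stop, or that received answers are dropped. The reminders are described for all four time points, and censoring may mean only that data are kept up to the last contact. This stands as a limit on the claim. It does not remove the need for a correction, because staff who follow the sentence as written would stop contacting the child.

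The scoring sentence is garbled. Since the sentence before it works form by form, it may mean only that a form must be complete for its own conversion. It therefore cannot be held up as a rule that withholds every T-score.

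The illustrations rest on assumed, independent rates. If the same families stay unreachable, few would have returned and the gap shrinks. If incomplete forms cluster in the same sittings, fewer assessments are lost. Even at 10% per visit about 33 of 50 remain, against the 32 that the plan's formula needs, so that scenario does not show a loss of planned power. Different loss by arm is possible in an unblinded trial. It is not shown: the contact procedure is the same for both arms, the data collectors are blinded, and the Discussion says control patients are also informed when scores cross a threshold.

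Finally, detailed handling of incomplete data often sits in a full protocol or analysis plan. That covers details such as the imputation model, but not a contact and loss rule that this article itself states.

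**Conclusion.** The concern holds as an unclear and badly fixed follow-up rule. Three unanswered calls within 24 h at one time point class a child as lost and censored, with no provision for return. Censoring is undefined for these endpoints, and the literal reading conflicts with the stated analysis of all available data. The scoring sentence is ambiguous and needs rewording, but is not shown to be wrong in intent.

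The size depends on an unreachable rate that the document does not give. Under independence it runs from small at 2% per visit (92% against 98% retained) to considerable at 10% (66% against 90%). The planned 20% loss is reached at about 5.4% per visit. Among the rates tried, power from observed month-12 data falls below 80% only at 15%. The documents do not establish that later or partial data will be thrown away, that planned power will be lost, or that loss will differ by arm. The change is still worth making before more follow-up passes, because uncollected questionnaires cannot be recovered.

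**What to change.** In Intervention and Control, replace the censoring clause with wording such as: *A questionnaire not obtained after the reminders and calls is recorded as missing for that time point only. The child stays in the study and is contacted at all later time points unless consent is withdrawn.*

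In Primary Outcome, reword the completeness sentence: *The T-score of each form is computed whenever that form is complete, regardless of the other forms.* If the primary outcome averages over forms, add how an assessment with some incomplete forms enters that average.

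Both changes agree with the analysis of all available data, and multiple imputation is then left for values that could not be obtained. The cost is two or three sentences and a few more calls at later visits. The automatic reminders simply continue.

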### Outcomes and Measurement

#### Primary Outcome

The primary outcome of this study is the mean T-scores of patients in the ePROs-based group and the control group. The C-Ped-PROMIS is the primary ePRO tool, and it has eight short forms for assessing the child's symptoms and quality of life during the previous 7 days. Each form has a single dimension, and the 5-level Likert scoring method scale with the answers “never” (0) and “almost” always (4) is used for each item. Raw scores of each form are converted to standardized T-scores with a mean of 50 and a standard deviation of 10. Only all forms are answered completely and performed this conversion.

#### Secondary Outcomes

The second outcomes of our study are the trajectories of C-Ped-PROMIS and HRQOL. We assessed the longitudinal changing trend of the mean T-scores of the C-Ped-PROMIS and the mean score of the PedsQL^TM^3.0-RM from baseline to 12 months after discharge. Furthermore, we examined the relationships between changes in C-Ped-PROMIS and changes in the HRQOL by evaluating the T-scores changes and PedsQL^TM^3.0-RM score changes among patients in the ePROs-based group and those in the control group.

The PedsQL^TM^3.0-RM (33) is a mature and specific tool for measuring the HRQOL of children with rheumatic diseases. It includes an age scale with five dimensions: pain (four items), daily activities (five items), treatment (seven items), worry (three items), and communication (three items), 22 items in total. There are five response options: “never,” “almost never,” “sometimes,” “almost always,” “always,” to which the scores 100, 75, 50, 25, and 0 are given, respectively. The scores of each dimension and total scale are the total score of each item divided by the number of response items, the score ranges from 0 to100, with higher scores indicating better HRQOL. The Chinese version of PedsQL^TM^3.0-RM has been verified to be a good instrument with acceptable reliability and validity and is suitable for assessing the quality of life among Chinese children with RA (37).

#### Other Data

The patient's disease-associated will be assessed through a separate disease-associated assessment questionnaire. Disease activity will be assessed by the JADAS, which includes the four measures and is feasible and possesses content validity. The presence or absence of complications, biochemical markers (erythrocyte sedimentation rate (ESR), C-reactive protein (CRP), tumor necrosis factor, and IL-1β), and laboratory tests (joint magnetic resonance imaging (MRI) and B-mode ultrasonography) are all recorded. During the initial assessment, a demographic questionnaire is sent to patients which included age, sex, race, ethnicity, and economic status. In addition, the completion time of the ePROs system, intervention compliance, and loss to follow-up will also be recorded.

### Statistical Analyses

SPSS 20.0 will be used for statistical analysis. Intention-to-treat analyses will be conducted by including all available data in the analysis. Missing data will be imputed by the multiple imputation method. A two-sided *p* < 0.05 is considered to be statistically significant. Data are first subjected to the normality tests, continuous variables that conformed to the normal distribution will be presented as the mean (SD), and do not conform to a normal distribution will be expressed as median (IQR). Categorical variables will be presented as frequencies or proportions. Comparisons between groups will be conducted using the Wilcoxon and Fisher's exact tests. Trajectories of PROs will be compared in two groups by repeated measures ANCOVA, as implemented under the general linear model. The MPLUS will be used to sort and analyze the data, and the LTA model was used to evaluate the intervention effect. In addition, subgroup analysis was carried out according to subgroups of JIA.

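### The LTA model said to evaluate the intervention effect does not estimate the between-arm T-score difference on which the trial is defined and sized

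*Protocol article*

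**What the plan says.** Statistical Analyses names Wilcoxon and Fisher's exact tests for group comparisons and repeated measures ANCOVA for trajectories. It then says that MPLUS will be used and that "the LTA model was used to evaluate the intervention effect". In that section only LTA is linked to the intervention effect in words. The abbreviation is never spelled out. The article gives no number of statuses, no indicators, and no statement of which LTA quantity would be read as the effect.

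Elsewhere the trial is built on means. The Objectives section makes the primary objective a between-group comparison of C-Ped-PROMIS T-scores. Under Primary Outcome, "The primary outcome of this study is the mean T-scores of patients" in the two groups. Sample Size Calculation uses a two-means formula, in which the mean ± SD "of ePRO group is 50 ± 10" and that "of the control group is 43 ± 10". It then says "Taking into account the dropouts and lost follow-up rate of about 20" per cent, "we will finally enroll 50 participants in each group". The secondary outcomes are trajectories of mean scores and the relationship between changes in two scores. None of these is a latent status or a transition between statuses.

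**The concern.** A latent transition model sorts children into symptom statuses at each visit and models the chance of moving between them. Whatever arm effect it gives is on status membership or on transitions, not on a mean T-score. If the sentence is followed as written, the claim about the intervention would rest on a quantity that the trial neither defined as an outcome nor was sized for, and whose value depends on how many statuses the analyst keeps.

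Two further risks depend on how the model is used. Dividing 40 to 50 children per arm by origin status leaves few children per comparison. And where a transition starts at a follow-up visit, its origin status may already have been changed by the intervention, so comparing arms within that status is no longer a randomised comparison.

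**Working it through.** **Inputs from the article.** 50 per arm enrolled, 1:1; dropout about 20%, so 50 × 0.8 = 40 remain; z values 1.96 and 0.84; "A two-sided *p* < 0.05 is considered to be statistically significant"; difference 50 − 43 = 7, SD 10; eight short forms; five visits, so four intervals.

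**Assumptions, not in the article.** S = 2, 3 or 4 statuses, equally filled at the start of an interval; probability of staying 0.6 to 0.8; statuses known without error, which favours LTA.

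**1. The plan's own figure.** n = (1.96 + 0.84)² × (100 + 100) × 2 / (2 × 7²) = 32 per arm, and 32/0.8 = 40. The stated 50 is not reproduced (dividing by 0.8 twice gives it). That is a separate matter and errs upward. The range 40 to 50 per arm is used below.

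**2. Power of the T-score contrast.** Φ(7/√(200/n) − 1.96) = 0.88 at n = 40 and 0.94 at n = 50.

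**3. Detectable difference in one transition, one interval.** Take k = n/S children per arm in an origin status and p₁ = 0.30. Find the smallest d with d/√[(p₁q₁ + p₂q₂)/k] ≥ 2.8. For n = 40, S = 2: k = 20, p₂ = 0.705, standard error √[(0.210 + 0.208)/20] = 0.1446, and 0.405/0.1446 = 2.80.

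| n per arm | S | k, one interval | d | 4k, four intervals | d |
|---|---|---|---|---|---|
| 40 | 2 | 20 | 0.41 | 80 | 0.21 |
| 50 | 2 | 25 | 0.37 | 100 | 0.19 |
| 40 | 3 | 13.3 | 0.48 | 53.3 | 0.26 |
| 50 | 3 | 16.7 | 0.44 | 66.7 | 0.23 |

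The last two columns hold one arm effect common over all four intervals and treat transitions as independent.

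**4. The same 7-point effect seen as a status.** Cutting two normal curves 0.7 SD apart at their midpoint gives 36% vs 64%. Within one origin status and one interval (pooled-variance test), power is 0.41–0.49 for S = 2 and 0.29–0.35 for S = 3, against 0.88–0.94 in step 2.

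**5. Cell sizes per arm and interval.** The expected off-diagonal count is (n/S)(1 − stay)/(S − 1). The chance of an empty cell is simulated.

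| S | Off-diagonal count | Chance that some off-diagonal cell is empty |
|---|---|---|
| 2 | 4–10 | 0–3% |
| 3 | 1.3–3.3 | 17–84% |
| 4 | 0.7–1.7 | 93–100% |

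**6. Parameter count.** If all eight forms are indicators, measurement is invariant and transitions are free over time: 8S + 8 + (S − 1) + 4S(S − 1), plus 4(S − 1) or 4S(S − 1) arm effects. This gives 37–41, 66–82 and 103–139 for S = 2, 3 and 4, against 80 to 100 children.

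**7. Conditioning on a follow-up status.** In a simulation with two statuses, an unmeasured severity factor influences status, the intervention acts only up to month 1, and there is no true effect from month 1 to 3. With severity SD 1.5 on the logit scale and an early effect of 1.0 or 1.5 log-odds, children in the low-symptom status at month 1 relapse by month 3 in 25.8% of controls and in 30.2% or 32.1% of treated children. Over severity SD 1 to 2 the spurious difference is about 2 to 7 points. It is zero when there is no unmeasured severity. Within baseline status the arms remain balanced on severity.

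**The case against.** The strongest reply is that the Objectives section already ties the effect of the intervention to the T-score comparison, that Primary Outcome confirms it, and that nothing calls LTA primary. The LTA sentence follows the one on trajectories and may describe a supplementary longitudinal analysis. This stands: a reader might infer that LTA is the primary analysis, and the article does not support that. What remains is that Statistical Analyses, where the methods are fixed, attaches the intervention effect to a different model.

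The number of statuses, the indicators and the constraints may lie in a fuller document, so their absence here is no fault. A reader might infer that the transition cells are certainly too sparse. With two statuses and frequent change they hold about 8 to 10 children or more, and at S = 2, 24 of the 37–41 parameters are measurement means and variances. Sparsity is a fair charge only from three statuses upward. An arm effect common to all intervals also roughly halves the detectable difference.

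Finally, a reader might infer that randomisation is lost from month 1 onward in any case. That holds only for arm effects on transitions starting at a follow-up visit. It does not touch baseline-to-month-1 transitions or status prevalence by arm, and the article does not say which would be used. The simulation also lets the intervention act only early, whereas Intervention and Control describes alerts triggered by questionnaires that continue to month 12. A bias of 2 to 7 points is well below what the trial could detect, so it would seldom stand out from noise.

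**Conclusion.** The point holds in a limited form. The model named for the intervention effect does not estimate the mean T-score difference in the objective, the primary outcome and the sample size. That mismatch needs no assumption beyond reading LTA as latent transition analysis, which is likely but inferred.

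The size claims are conditional. With two or three equally filled statuses known without error, LTA could detect about 37 to 48 points from 30% in a single interval, or about 19 to 26 with a common effect over four intervals. The T-score contrast has power of 0.88 to 0.94 for the planned difference. With three or more statuses, many transition cells would be very small or empty. The spurious later difference of about 2 to 7 points arises only if arm effects are reported on transitions starting at month 1 or later, and only with unmeasured severity (SD 1 to 2 logits assumed). The article does not show that such effects are planned, so this is a use to rule out and not an error already made.

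**What to change.** In Statistical Analyses, replace the LTA clause with two statements. First, the intervention effect is evaluated by the randomised between-arm contrast of C-Ped-PROMIS T-scores given under Objectives and Primary Outcome. Second, LTA (written out in full) is exploratory. If LTA results are compared by arm, report only status membership at each visit by arm, either marginally or conditional on baseline status. Show no arm effect on transitions that start at a follow-up visit.

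The cost is about two sentences. Data collection and sample size do not change, and LTA can still be run and published. The downside is that no inferential claim rests on it.
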